### Interim analyses {21b}

After termination of the radiation treatment of one third (N = 56) and two thirds (N = 112), respectively, of the patients, interim analyses will be performed. Recruitment will be put on hold until the 56 and 112 patients, respectively, have completed their radiation treatment. In case of a dissatisfaction rate > 25%, the reminder app needs to be modified and adapted. In case of a dissatisfaction rate > 50%, the study will be terminated prematurely.

### Methods for additional analyses (e.g., subgroup analyses) {20b}

Not applicable.

### Methods in analysis to handle protocol nonadherence and any statistical methods to handle missing data {20c}

The full analysis set includes all randomized patients who have started either therapy with Arm A or with Arm B. The full analysis set will be analyzed according to the intent-to-treat principle, i.e., patients will be analyzed in their initial group of randomization.

The per protocol set will comprise all patients of the full analysis set and will exclude patients if any of the following criteria are met:
Administration of less than 60 Gy if the reason for discontinuation was any other than death or unacceptable toxicityDelay of radiotherapy for more than 7 days prior to reaching 60 Gy

All patients in the per protocol set will be analyzed within their group of actual treatment received.

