## Introduction

### Background and rationale {6a}

Many patients with squamous cell carcinoma of the head and neck (SCCHN), particularly those patients with locally advanced disease, receive radiotherapy. If radiotherapy is administered as definitive treatment (i.e*.*, without preceding surgery), it is generally combined with chemotherapy [1]. In an adjuvant situation (i.e*.*,following surgery), concurrent chemotherapy will be administered if risk factors (incomplete resection and/or extracapsular [ECS] spread of lymph nodes metastases) exist.

Radiotherapy of SCCHN can be associated with significant toxicities including dermatitis and oral mucositis. Severe toxicities may require interruptions of the radiotherapy series that can impair the prognoses of these patients [2, 3]. To avoid severe (grade ≥ 3) radiation toxicities, it is important to avoid or postpone grade 2 toxicities. Grade ≥ 2 dermatitis and grade ≥ 2 mucositis rates were very high in previous studies (86–92% and 86–100%, respectively) and require improvement [4–6]. In the previous RAREST-01 trial that compared the dressing Mepitel® Film to standard skin care in patients irradiated for head-and-neck cancer, dermatitis rates were lower than expected in both groups [7, 8]. In the RAREST-01 trial, standard skin care was supposed to be performed four times daily, which required a high level of discipline from the patients. Daily reminders by medical staff members regarding the importance of skin care likely improved the patients’ compliance resulting in less radiation dermatitis. It may be questioned whether the daily reminders by staff members can be replaced by a mobile application (a reminder app).

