### Intervention description {11a}

#### Standard skin care

In both the experimental (A) and the control arm (B), standard skin care is to be performed by the patient from the beginning of radiotherapy. Standard skin care may vary at the participating centers. At the University of Lübeck, it includes fatty cream with 2–5% urea (fatty cream alone, if patients do not tolerate urea) and mometasone furoate cream. The treatment will be continued until 1 week after EOT or until a patient experiences grade ≥ 2 moist desquamation or grade ≥ 3 radiation dermatitis.

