## Assignment of interventions: blinding

### Who will be blinded {17a}

Data analysts and statisticians will be blinded.

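### Two per-protocol rules, grouping by treatment received and excluding every radiotherapy delay over 7 days, can bias the supportive per-protocol analysis

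*Protocol article*

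**What the plan says.** All the rules stand in the protocol article, section {20c} (nonadherence and missing data).

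- **Full analysis set.** It comprises "all randomized patients who have started either therapy with Arm A or with Arm B". It follows the intent-to-treat principle: "patients will be analyzed in their initial group of randomization". It has no exclusion for delay or toxicity.
- **Per-protocol set, dose rule.** Patients of the full analysis set who received less than 60 Gy are excluded, except where the reason was death or unacceptable toxicity.
- **Per-protocol set, delay rule.** Patients with a delay of more than 7 days before 60 Gy are excluded. No reason is exempt.
- **Per-protocol set, grouping.** "All patients in the per protocol set will be analyzed within their group of actual treatment received".

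The article does not name the primary analysis set outright. Sample size {14} counts its 80 patients per arm in the full analysis set, so the per-protocol set reads as supportive.

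**The concern.** **Grouping.** In both arms "standard skin care is to be performed by the patient from the beginning of radiotherapy", and mouth care is likewise common to both. Arm A adds only the app. An Arm A patient who does not use it has received what Arm B receives, and grouping by treatment received could count that patient in Arm B. Neither per-protocol exclusion concerns app use, so such patients are not removed beforehand. Background {6a} and the Discussion suggest that discipline with skin care lowers dermatitis. Non-users are therefore plausibly at higher risk, and moving them would improve Arm A and worsen Arm B even if the app did nothing.

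**Delay.** Background {6a} states: "Severe toxicities may require interruptions of the radiotherapy series that can impair the prognoses of these patients". A long delay can thus be a consequence of the toxicity that the trial measures. A patient who stops for toxicity stays in the set, while one who pauses for 8 days for the same toxicity leaves it. The two neighbouring rules conflict in logic, and the second selects on the outcome.

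**At stake** is whether the per-protocol result can be read as support for the main comparison. A lesser question is what 'started' means in the full analysis set. If it meant opening the app, only Arm A patients could fail it.

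**Working it through.** **Inputs from the article.** Control rate 85%, chi-square test, two-sided 5%, 80% power, 80 per arm in the full analysis set, 5% loss, 168 randomised (Sample size {14}). I read the 20% reduction as points, giving 85% v 65%.

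**The plan's own figure.** At 80 per arm and 85% v 65%, exact power is 79.9% with Fisher's test and 84.8% with the uncorrected chi-square test. So 80 is reproduced with Fisher's test. For the total, 160 × 1.05 = 168. None of these figures is in dispute here. The article gives no rate of app non-use, delay or non-start, so every shift below is illustrative.

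**(a) Grouping by treatment received, no true effect.** Both arms have a true rate of 85%. A share x of Arm A, with event rate r, is moved to Arm B:

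- Arm A becomes (0.85 − x·r)/(1 − x)
- Arm B becomes (0.85 + x·r)/(1 + x)

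The false-rejection rate is a two-sided normal approximation at the 5% level, with 80(1 − x) and 80(1 + x) patients.

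| x | r | Arm A | Arm B | A − B (points) | False rejection, about |
|---|---|---|---|---|---|
| 5% | 90% | 84.7% | 85.2% | −0.5 | 5.1% |
| 10% | 90% | 84.4% | 85.5% | −1.0 | 5.4% |
| 20% | 90% | 83.8% | 85.8% | −2.1 | 6.8% |
| 5% | 100% | 84.2% | 85.7% | −1.5 | 5.9% |
| 10% | 100% | 83.3% | 86.4% | −3.0 | 8.5% |
| 20% | 100% | 81.3% | 87.5% | −6.3 | 19.9% |

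If non-users have the same 85% rate as everyone else, both formulas return 85% and the shift is zero. The bias depends on non-users being at higher risk.

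**(b) Delay rule, primary endpoint.** Suppose all excluded patients had grade ≥ 2 dermatitis. With shares f_A and f_B excluded, each arm's rate becomes (p − f)/(1 − f).

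| True rates A v B | f_A / f_B | Arm A | Arm B | B − A (points) |
|---|---|---|---|---|
| 85% v 85% | 2% / 8% | 84.7% | 83.7% | −1.0 |
| 65% v 85% | 2% / 8% | 64.3% | 83.7% | 19.4 |
| 65% v 85% | 5% / 10% | 63.2% | 83.3% | 20.2 |
| 65% v 85% | 5% / 5% | 63.2% | 84.2% | 21.1 |

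A true 20-point effect can shrink or grow. With no effect, the first row makes the app look slightly harmful.

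**(b) Delay rule, grade ≥ 3 (secondary).** Assume 30% in Arm B and 15% in Arm A, with half of these patients delayed by more than 7 days:

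- Arm B: (0.30 − 0.15)/(1 − 0.15) = 17.6%
- Arm A: (0.15 − 0.075)/(1 − 0.075) = 8.1%

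The risk difference falls from 15 to 9.5 points. The odds ratio stays at (0.30/0.70)/(0.15/0.85) = 2.43, and the risk ratio rises from 2.00 to 0.1765/0.0811 = 2.18.

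**(c) 'Started' in the full analysis set.** Take the extreme case in which all 8 lost patients (5% of 168, rounded) come from Arm A's 84, with true rates of 85% in both arms. The shift is (71.4 − 8r)/76 − 0.85, where 71.4 = 84 × 0.85. It is −1.6 points at r = 100%, 0 at 85%, +2.1 at 65% and +8.9 at 0%. If 4 are lost per arm at the same event rate, there is no shift.

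**The case against.** The strongest reply is that the main comparison is untouched. The full analysis set is grouped as randomised and keeps every delayed patient, so no severe toxicity disappears from the trial's results. That stands, and it confines the point to the per-protocol set.

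It is also fair to say that the article does not state that a non-user has received Arm B, so regrouping is a possible reading and not a certain one. Eligibility {10} requires the ability to use a smartphone and excludes expected noncompliance, which makes 20% non-use a high assumption. At 5–10% the false benefit is 0.5 to 3.0 points and false rejection 5.1–8.5%. An unseen analysis plan may define both terms more closely. But the grouping and delay rules are written out in the article, so they are not merely omissions left to that plan.

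A reader might infer three stronger claims, which the documents do not support.

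- *Both analysis sets are biased.* For the full analysis set this would need 'started' to mean opening the app. The article does not say so. It could equally mean the standard care or radiotherapy common to both arms, and even on the app reading the direction is not fixed, as (c) shows. On that reading, too, patients who never opened the app would be outside both sets and could not be regrouped, so the two mechanisms cannot both apply to them.
- *The delay rule always dilutes the effect.* On the primary endpoint it can go either way. In the grade ≥ 3 example the risk difference falls, but the odds ratio does not change.
- *The rules always favour the app.* Only the regrouping does, and only if non-users are at higher risk.

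**Conclusion.** The point holds for the per-protocol set. Grouping by treatment received gives up randomisation. With no true effect, 5–20% non-use and event rates of 90–100% in non-users, it creates a false benefit of about 0.5 to 6 points. The delay rule selects on toxicity and is inconsistent with the exemption in the dose rule beside it. Its effect on the primary endpoint was about 1 point either way in the cases tried, with no fixed direction. All sizes rest on assumed rates.

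The full analysis set, on which the trial is sized, is not shown to be biased. Its undefined 'started' is a wording gap worth closing, no more. The matter should be corrected because a per-protocol analysis built this way cannot be relied on to support the main one, but it does not threaten the main comparison.

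**What to change.** 1. Analyse the per-protocol set by randomised arm. Do not replace the regrouping with an exclusion of app non-users from Arm A, because that is still a one-sided selection. With 20% non-users at 95% or 100%, Arm A users would stand at 82.5% or 81.25% against 85% in Arm B. That is a false benefit of 2.5 or 3.75 points, against 4.2 or 6.25 with regrouping. The article also describes no usage log beyond patients' own statements in the app.
2. Give the delay criterion the same exemption as the dose criterion: exclude only delays not due to toxicity or death. The reason for a delay must then be recorded, as the dose rule already requires for stopping.
3. As a lesser point, tie 'started' in the full analysis set to an event common to both arms, for example the first radiotherapy fraction, regardless of app use.

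The cost is wording in the protocol and the analysis plan, which section {20a} says will be finalised before database lock. The per-protocol estimate may be slightly less favourable to the app, and it will no longer describe those who used the app as a separate group.

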### Plans to give access to the full protocol, participant level-data and statistical code {31c}

Not applicable.

## Oversight and monitoring

### Composition of the coordinating center and trial steering committee {5d}

Not applicable.

### Composition of the data monitoring committee, its role and reporting structure {21a}

A data monitoring committee is not needed, since all patients participating in this trial receive the same anticancer treatment, the same number and type of visits, and the same treatment for radiation dermatitis, oral mucositis and other toxicities as they would have received if not participating in the trial.

### Adverse event reporting and harms {22}

#### Assessment and documentation of adverse events

The severity of adverse events should be assessed using the national (CTCAE, version 5.0 [9]. Oral mucositis will be assessed according to the criteria of the Radiation Therapy Oncology Group (RTOG) [10–13].

Otherwise, the 5-point scale below will be used to describe an adverse event.

Scale: 1 = mild, 2 = moderate, 3 = severe, 4 = life-threatening and 5 = fatal.

The following scale should be used to describe the likelihood that the event was caused by the trial treatment:

1 = certain/definite, 2 = probable, 3 = possible, 4 = unlikely, 5 = not related, 6 = not assessable.

#### Reporting of serious adverse events and unexpected adverse events

Serious adverse events and unexpected adverse events must be reported within 24 hours after their detection/onset by fax to the coordinating investigator.

### Frequency and plans for auditing trial conduct {23}

The ZKS Lübeck will conduct clinical on-site monitoring at the German sites according to Good Clinical Practice (GCP) and written SOPs to ensure the patients’ rights and safety as well as the reliability of trial results. For initiation, trial sites will be visited on-site by a clinical research associate of the ZKS Lübeck. During the trial, sites will be visited at regular intervals depending on the rate of recruiting and data quality. Informed consent and defined key data will be checked of all patients. The medical file of each patient will be screened for adverse and serious adverse events. Patients’ questionnaires will be checked for their existence. According to SOPs, all trial-specific monitoring activities will be defined before starting the trial and documented in writing (monitoring manual). The sites in other countries will be monitored according to the corresponding national regulations. No regular audits are planned. However, to ensure correct execution of the study, audits may be conducted if necessary. As the current study is not linked to any German pharmaceutical or medicinal product act, no inspections of higher federal authorities are scheduled.

### Plans for communicating important protocol amendments to relevant parties (e.g. trial participants, ethical committees) {25}

Amendments to the study protocol may only be implemented if approved again by the ethics committee responsible. Only the coordinating principal investigator may carry out such changes. However, all co-investigators should contact the coordinating principal investigator if modifications seem to be necessary. In case of changes to the study protocol, all investigators will be informed after ethics committee approval and the notice will have to be confirmed.

## Dissemination plans {31a}

The coordinating principal investigator will work toward comprehensive internal and external dissemination of project results and knowledge. Coordinating principal investigators, biostatisticians, and reference centers will create a report according to the CONSORT statement regardless of regular or abnormal study termination. The scientific results will be published in international, peer-reviewed journals of the highest possible quality. In addition, results will be presented at major medical congresses and symposia.

Due to methodological and statistical aspects, results will be published only after study database closure. All reports and publications related to the study need to be coordinated with the biostatistician to avoid misinterpretation of statistical results. Conclusions need to be statistically secured and require approval of the statistician. The local centers are entitled to use the recorded data for additional scientific exploitation under their own name, but not before the main results have been published. There are no exceptions to this rule. Any sub-publication requires approval by the coordinating principal investigator. For publications of any kind the study acronym RAREST-02 will be used.

## Discussion

Many patients who receive radiotherapy or radio-chemotherapy for locally advanced SCCHN experience radiation-related acute toxicities including dermatitis and oral mucositis. If these toxicities become severe, an interruption of the radiotherapy treatment may be required. Interruptions of 1 week or longer were reported to impair the patient’s prognosis. In a retrospective study of patients irradiated for SCCHN, local control (*p* = 0.015) and survival (*p* = 0.021) were significantly worse with such an interruption of the radiation treatment [2]. To avoid toxicity-related interruptions of radiotherapy, it is reasonable to avoid or at least postpone grade 2 reactions. This accounts for both radiation dermatitis and radiation-related oral mucositis. In previous studies of radio-(chemo)-therapy for SCCHN, rates of grade ≥ 2 radiation dermatitis and grade ≥ 2 oral mucositis were reported to range from 86% to 92% and from 86% to 100%, respectively, although the patients had received standard skin and mouth care [1, 4–6].

Since the administration of an absorbent, self-adhesive dressing appeared a promising approach to reduce radiation dermatitis, we performed a randomized trial (RAREST-01) that compared the new dressing Mepitel® Film to standard skin care with respect to radiation dermatitis rates [7, 8]. However, almost half of the patients did not tolerate the dressing, and the trial had to be stopped prematurely. In those patients already included, the new dressing appeared to be not superior to standard skin care. Surprisingly, the radiation dermatitis rates were lower than expected in both groups. One possible explanation for this unexpected finding could be that the patients were reminded daily by staff members to perform their skin care, which generally required a high level of discipline and compliance. Improved compliance of patients resulting in a proper performance of daily skin care might have led to a lower incidence and severity of radiation dermatitis. One question is whether the daily reminders by the staff members can also be successfully done by a specific reminder app. Therefore, in this trial the effect of a reminder app on radiation dermatitis rates and, additionally, on oral mucositis rates is being investigated. If the addition of such a reminder app to standard care leads to less radiation dermatitis and oral mucositis, it could become a helpful tool for patients irradiated for head-and-neck cancers.

## Trial status

Protocol version 2.0 from 09-30-2019, recruitment is planned to start in December 2019 and will be completed within 24 months.

## Data Availability

Not applicable, as no datasets were generated or analyzed during the current study so far. The study has been registered at clinicaltrials.gov (identifier: NCT04110977), where details of the study protocol presented in this manuscript are available.

## Abbreviations

CTCAE: Common Terminology Criteria for Adverse Events
ECS: extracapsular spread
EORTC: European Organisation for Research and Treatment of Cancer
EOT: end of radiation treatment
GCP: Good Clinical Practice
QLQ: Quality of Life Questionnaire
RTOG: Radiation Therapy Oncology Group
SCCHN: squamous cell carcinoma of the head and neck
SOP: standard operating procedure
